### Statistical considerations

#### Power

The reported mean rSO_2_ is 67.1% ± 6.2 for patients placed in beach chair position
[7]. Based on a previous investigation
[11], we expect a 6–8 percentage point difference in rSO_2_ resultant upon the planned change in FIO_2_ and a 2–4 percentage point difference resultant upon the planned change in PETCO_2_. A total percentage point increase in excess of 10 would be of clinical significance. A sample size of 48 will have a power of greater than 0.8 to detect a 4-5% in the planned pairwise comparisons. Allowing for an approximately 10% drop out 54 subjects will be recruited, targeting 24 patients in each group randomized to an anesthetic. The power for the comparison between the two anesthetic regimens is better than 85% for a difference of 6% which would be a clinically important difference for the secondary outcome.

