**Methods/design:**

This is a prospective within-group study of patients undergoing shoulder arthroscopy in the beach chair position which incorporates a randomized comparison between two anesthetics, approved by the Institutional Review Board of the University of Michigan, Ann Arbor. The primary outcome measure is the change in regional cerebral oxygenation due to sequential changes in oxygenation and ventilation. A sample size of 48 will have greater than 80% power to detect an absolute 4-5% difference in regional cerebral oxygenation caused by changes in ventilation strategy. The secondary outcome is the effect of anesthetic choice on cerebral desaturation in the beach chair position or response to changes in ventilation strategy. Fifty-four patients will be recruited, allowing for drop out, targeting 24 patients in each group randomized to an anesthetic. Regional cerebral oxygenation will be measured using the INVOS 5100C monitor (Covidien, Boulder, CO). Following induction of anesthesia, intubation and positioning, inspired oxygen fraction and minute ventilation will be sequentially adjusted. At each set point, regional cerebral oxygenation will be recorded and venous blood gas analysis performed. The overall statistical analysis will use a repeated measures analysis of variance with Tukey’s HSD procedure for post hoc contrasts.

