The study described here will test the hypothesis that the manipulation of inspired oxygen fraction and end tidal carbon dioxide leads to significant changes in rSO_2_ in patients anesthetized in the beach chair position. The influence of anesthetic technique on this process will be tested as a secondary outcome.

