## Methods/design

This is a prospective within-group study with an additional randomized comparison of two anesthetic regimens (Figure
1). The study was approved by the Institutional Review Board of the University of Michigan, Ann Arbor. The primary aim is to determine the effect of increasing the FIO_2_ or PETCO_2_ on cerebral oxygen saturation in patients anesthetized in the beach chair position. Our secondary aim is to investigate the effects of differing anesthetic agents on cerebral oxygenation in patients placed in the beach chair position.

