#### Analysis

Data will be analyzed with a repeated measures two-way analysis of variance in which ventilation strategy is the within-subjects factor and anesthetic regimen is the between-subjects factor. Residuals will be assessed for normality and equal variances; if necessary, the analyses will be adjusted. The primary analysis will focus on the comparison between the ventilation strategies. A post hoc Tukey’s HSD procedure will be used to correct for all pairwise comparisons between ventilation strategies.

The effect of desflurane or propofol on cerebral desaturation and a possible differential response to changes in ventilation strategy will be evaluated as a secondary outcome measure. Analysis for the primary outcome will be adjusted if interaction effects between ventilation strategy and the anesthetic used are significant. A p value of <0.05 will be considered statistically significant.

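### The stated power (above 0.8 for 4-5 points) meets the expected PETCO2 effect of 2-4 points only at its upper edge, although PETCO2 is part of the primary hypothesis

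*Protocol article*

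**What the plan says.** The hypothesis at the end of the Background is that "the manipulation of inspired oxygen fraction and end tidal carbon dioxide leads to significant changes in rSO_2". Methods/design repeats the pairing: "The primary aim is to determine the effect of increasing the FIO_2_ or PETCO_2_ on cerebral oxygen saturation". Both gas changes are thus primary.

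The Power section gives an SD of 6.2 for rSO2 in the beach chair position. It expects 6-8 points from the FIO2 change and "a 2–4 percentage point difference resultant upon the planned change in PETCO_2" (percentage points of rSO2). It then states: "A sample size of 48 will have a power of greater than 0.8 to detect a 4-5% in the planned pairwise comparisons". The abstract confirms that absolute points are meant: "greater than 80% power to detect an absolute 4-5% difference in regional cerebral oxygenation caused by changes in ventilation strategy".

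Methods/design lists five set points. Step 3 against step 2 changes FIO2 alone. Step 4 against step 3 changes PETCO2 alone. The Analysis section does not single out these two. It says that a post hoc Tukey "HSD procedure will be used to correct for all pairwise comparisons between ventilation strategies".

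**The concern.** The power statement is worded for the planned pairwise comparisons as a group, and one of the two comparisons that carry the hypothesis is expected to be smaller than the difference powered for. The ranges 4-5 and 2-4 touch only at 4. For an expected effect from 2 to just under 4 points the plan makes no power claim.

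The risk is in the reading of results. If the PETCO2 comparison is not significant, a reader who remembers power above 80% may take it as evidence that PETCO2 has little effect, although the trial was not stated to be powered for the effect it expected. Correcting over all pairs also applies a stricter threshold to the smaller primary effect than the two-part hypothesis requires.

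**Working it through.** **Inputs from the protocol.** n = 48; SD = 6.2, a between-patient value in one position; significance level 0.05, taken as two-sided; five set points, giving 5 × 4 / 2 = 10 pairs (6 if only the four beach chair set points count). **Assumed:** the within-patient correlation ρ, which the article does not give.

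**Formulas.** SD of a within-patient difference = 6.2 × √(2(1 − ρ)). Noncentrality = δ × √48 / SD of difference. Power comes from the noncentral t distribution. The critical |t| is 2.01 unadjusted (47 df). With Tukey over five set points it is q(0.95; 5, 184)/√2 = 2.755, a per-pair level of about 0.0065. Tukey over four set points gives 2.60 (138 df).

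**Reproducing the plan's figure.** At ρ = 0 the SD of the difference is 6.2 × √2 = 8.77 and the standard error is 8.77/√48 = 1.27.

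- Unadjusted: power 0.87 at 4 points and 0.97 at 5; difference detectable with 80% power, 3.62.
- Tukey, five set points: power 0.66 at 4 points and 0.88 at 5; detectable difference 4.56 (4.36 over four set points).

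Power above 0.8 for 4-5 points therefore agrees with the plan's own inputs. The Tukey value of 4.56 lies inside the stated 4-5 and the unadjusted 3.62 lies below it, so the figure may already include the correction. The text does not say. Recruitment also checks: 48/(1 − 0.10) = 53.3, rounded up to 54.

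**Power for the PETCO2 contrast, n = 48.**

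| ρ | Test | 2 points | 3 points | 4 points |
|---|---|---|---|---|
| 0 | Tukey, 5 set points | 0.123 | 0.353 | 0.657 |
| 0 | Unadjusted | 0.34 | 0.64 | 0.87 |
| 0.5 | Tukey, 5 set points | 0.305 | 0.724 | 0.956 |
| 0.5 | Unadjusted | 0.59 | 0.91 | 0.99 |
| 0.7 | Tukey, 5 set points | 0.553 | 0.941 | 0.999 |
| 0.7 | Unadjusted | 0.81 | 0.99 | >0.99 |

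Under Tukey over five set points, 80% power needs ρ of at least about 0.81 for 2 points, 0.57 for 3 and 0.23 for 4. Counting only the four beach chair set points changes little: at ρ = 0.5 the powers are 0.361, 0.773 and 0.968.

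**Two named contrasts instead of all pairs, ρ = 0.5.** Bonferroni over two gives 0.47 at 2 points and 0.85 at 3. A fixed sequence with FIO2 first gives 0.59 and 0.91. These equal the unadjusted values because the FIO2 test is almost certain to pass at 6-8 points. Holm then performs almost the same, since once FIO2 is rejected PETCO2 is also tested at 0.05.

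**The case against.** **The sample size is not wrong.** The 48, the 54 and the power above 0.8 all reproduce, and the FIO2 effect of 6-8 points is covered. The abstract and the Power section both attach the claim to 4-5 points, and neither promises 80% power at 2 or 3. This stands.

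**Tukey may not be a further loss.** A reader might infer that the correction pushes power below the stated figure. The documents do not support that, because the figure may already include it. On that reading, though, the detectable difference at ρ = 0 (4.56) lies above the whole 2-4 range, so the gap in coverage remains.

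**Tukey is a valid choice.** It controls error over all pairs and suits the Discussion's wish to find the best ventilation strategy. It is not an error. The case for two named contrasts is that they match the stated hypothesis and gain power on its weaker part.

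**The correlation is unknown.** A reader might infer that a null PETCO2 result would probably be a power failure. That cannot be said: at 3 points, Tukey power runs from 35% at ρ = 0 to 94% at ρ = 0.7. A condensed article may also leave the SD of change to the full protocol, so its absence is not the fault here.

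**The 10-point criterion.** The Power section adds: "A total percentage point increase in excess of 10 would be of clinical significance". A reader might infer that no comparison addresses this, or that a significant 5-point effect would fall short of it. Neither holds. Step 4 against step 2 is one of the all-pairs comparisons and measures the combined rise, expected at 6 + 2 = 8 to 8 + 4 = 12 points. The criterion applies to the total, not to one component.

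**Conclusion.** The point holds as a mismatch inside the Power section. The plan expects 2-4 points from a primary comparison and states power only for 4-5, so most of the expected PETCO2 range has no power claim. This rests on the protocol's own figures and needs no assumption.

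Its practical size depends on ρ. With SD 6.2 and Tukey over five set points, a 2-point effect has power below 60% up to ρ = 0.7. A 3-point effect is adequately powered from about ρ = 0.57, and a 4-point effect from about 0.23. The trial is not shown to be underpowered, and a null PETCO2 result could, but need not, reflect low power. The calculation applies the between-patient SD of 6.2 at every set point and a common correlation across set points.

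This deserves correction before results are interpreted. It does not invalidate the sample size or the analysis.

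**What to change.** 1. **Analysis section:** name two primary contrasts, step 3 minus step 2 (FIO2) and step 4 minus step 3 (PETCO2). Test them in fixed sequence with FIO2 first, or by Holm. Keep Tukey-adjusted comparisons of the remaining pairs, including step 4 minus step 2, as secondary.
2. **Power section and abstract:** state power separately for each primary contrast under the test to be used, with the assumed within-patient correlation. Say that power above 0.8 is not claimed for the lower part of the 2-4 point PETCO2 range.

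**Cost:** wording only, with no extra patients. The stated PETCO2 power becomes less favourable, and the other eight pairs become secondary. In a fixed sequence PETCO2 cannot be claimed if FIO2 fails, a small risk at the expected 6-8 points and one that Holm avoids.

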[19]. The relative effect of these agents when used as infusions has not been published and phenylephrine has been used as an infusion in other studies examining rSO_2_. Here, we will use ephedrine (5 mg) in preference to phenylephrine (50-100mcg) as an intravenous bolus medication for the treatment of intraoperative hypotension when heart rate is less than 80 beats per minute. Phenylephrine by infusion (200mcg/ml) will be titrated to maintain blood pressure within 20% of preoperative mean arterial pressure (MAP) when there has been a requirement for more than 400mcg of phenylephrine over a 20 min period. Pre-treatment with ephedrine significantly blunts the decrease in rSO_2_ seen with bolus phenylephrine for at least 20 min
[19]. If phenylephrine bolus dose is used as the first treatment for intraoperative hypotension we will delay the recording of results following a trial intervention by at least 8 min.

For MAPs greater than 70-80 mmHg associated with intraoperative bleeding the initial treatment will be to ensure adequate depth of anesthesia (BIS 40–60), followed by administration of incremental boluses of fentanyl 25mcg, up to a maximum dose of 2.5 mcg/kg. Failure of this to achieve the required reduction in blood pressure will result in the administration of the antihypertensive medications labetolol or hydralazine at the discretion of the patient’s anesthesiologist.

Standard American Society of Anesthesiologists monitoring will be used for all patients. The BIS Quatro electrode will be placed diagonally on the patient’s left forehead. Cerebral oxygenation will be measured using the INVOS 5100C monitor (Covidien, Boulder, CO). Optodes will be applied, before induction of anesthesia, by a single trained researcher on either side of the BIS Quatro sensor as recommended by the manufacturer.

Following induction of anesthesia, FIO_2_ and minute ventilation will be sequentially adjusted to achieve:

1) FIO_2_ 30% (70% nitrogen), PETCO_2_ 30 mmHg – supine position.

2) FIO_2_ 30% (70% nitrogen), PETCO_2_30mmHg – beach chair position.

3) FIO_2_ 100%, PETCO_2_ 30 mmHg – beach chair position.

4) FIO_2_ 100%, PETCO_2_ 45 mmHg – beach chair position.

5) FIO_2_ 30%, PETCO_2_ 30 mmHg – beach chair position.

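### Run classically over the five set points, the planned repeated measures ANOVA would drop a patient who lacks only set point 5; a mixed model would keep that patient's primary readings at almost no cost

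*Protocol article*

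**What the plan says.** **Sample size (protocol article, Power).** The study is powered on 48 patients: "A sample size of 48 will have a power of greater than 0.8 to detect a 4-5% in the planned pairwise comparisons". Recruitment is then raised: "Allowing for an approximately 10% drop out 54 subjects will be recruited, targeting 24 patients in each group randomized to an anesthetic".

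**Analysis (protocol article, Analysis).** "Data will be analyzed with a repeated measures two-way analysis of variance in which ventilation strategy is the within-subjects factor". The same model compares desflurane with propofol between patients. Tukey's HSD covers all pairwise comparisons of strategies. The section provides for adjusting the analysis if residuals are not normal, if variances are unequal, or if strategy and anesthetic interact. It does not say what happens to a patient with an incomplete sequence, and it does not list the levels of the within-subjects factor.

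**Sequence (protocol article, Methods/design).** There are five set points in fixed order. Set point 1 is supine and the rest are in the beach chair. Set points 1, 2 and 5 share FIO2 30% and PETCO2 30 mmHg. Set point 3 raises FIO2 to 100%. The next is "4) FIO_2_ 100%, PETCO_2_ 45 mmHg – beach chair position". The primary aim is the effect of raising FIO2 or PETCO2 in the beach chair position. A patient whose pulse oximetry stays below 95% on FIO2 30% is withdrawn and replaced; whether readings already taken are kept is not stated.

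**The concern.** The primary question is answered by two within-patient contrasts: set point 2 against 3 for FIO2, and 3 against 4 for PETCO2. Both are complete before set point 5, which returns to the starting ventilation. A patient who stops after set point 4 has therefore supplied everything the primary question needs.

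A classical repeated measures ANOVA works on complete rows: one missing level removes the patient. Set point 5 comes last, so any sequence that is cut short lacks it. With about 10% drop-out expected, the named method could discard primary readings already taken. It would also remove those randomized patients from the desflurane and propofol comparison, which uses the same model. At stake is efficiency, chiefly for PETCO2, the smaller of the two expected effects.

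**Working it through.** **Inputs from the protocol article**
- 48 evaluable, 54 recruited, about 10% drop-out (Power).
- Mean rSO2 67.1% with 6.2, read as the SD, "for patients placed in beach chair position" (Power).
- Expected effects (Power): 6 to 8 for the "percentage point difference in rSO_2_ resultant upon the planned change in FIO_2", and 2 to 4 for the "percentage point difference resultant upon the planned change in PETCO_2".
- Significance level: "A p value of <0.05 will be considered statistically significant" (Analysis); two-sided is assumed.

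**Assumed.** The within-patient correlation rho is not given; 0 to 0.7 is used.

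**Step 1: the plan's own figures.** 48/(1 − 0.10) = 53.3, rounded up to 54, as stated. For power, take SD of a difference = 6.2 × sqrt(2(1 − rho)) and a paired t test with n = 48. Without multiplicity adjustment and at rho = 0, power is 0.872 for 4 points and 0.972 for 5, so the stated power above 0.8 is reproduced. With Tukey over five set points it is 0.657 and 0.882 at rho = 0, and 0.845 and 0.974 at rho = 0.3.

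**Step 2: what a patient without set point 5 contributes**

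| Quantity | Set points needed | Available without set point 5? |
|---|---|---|
| FIO2 contrast | 2 and 3 | yes |
| PETCO2 contrast | 3 and 4 | yes |
| Classical ANOVA over five levels | 1 to 5 | no, patient dropped |

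**Step 3: gain in the standard error.** The expected loss is 54 − 48 = 6 patients (6/54 = 11.1%). The standard error of a within-patient contrast is proportional to 1/sqrt(n). If k of the six stop after set point 4 and are kept, the ratio is sqrt(48/(48 + k)):
- k = 6: sqrt(48/54) = 0.943, about 6% smaller (the ceiling)
- k = 3: sqrt(48/51) = 0.970, about 3% smaller
- k = 2: sqrt(48/50) = 0.980, about 2% smaller
- k = 0: no gain

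**Step 4: the ceiling in terms of power.** Noncentral t, Tukey critical value for five set points, error degrees of freedom (n − 2) × 4. Each cell shows n = 48 → n = 54.

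| True difference | rho 0 | rho 0.3 | rho 0.5 | rho 0.7 |
|---|---|---|---|---|
| 2 points | 0.123 → 0.144 | 0.197 → 0.230 | 0.305 → 0.354 | 0.553 → 0.621 |
| 3 points | 0.353 → 0.408 | 0.532 → 0.600 | 0.724 → 0.788 | 0.941 → 0.966 |
| 4 points | 0.657 → 0.725 | 0.845 → 0.894 | 0.956 → 0.976 | 0.999 → 1.000 |
| 5 points | 0.882 → 0.923 | 0.974 → 0.987 | 0.998 → 0.999 | 1.000 → 1.000 |

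The largest gain in the table is about 0.07. The 2- and 3-point rows lie within the range expected for PETCO2. For differences of 6 points or more, as expected for FIO2, power at n = 48 would be higher than in the 5-point row, so little is gained there.

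**The case against.** The case on the other side is substantial.

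- **The article never says that only complete sequences are analysed.** True. That follows from how the named method is classically run. Handling of missing data may sit in a full protocol or analysis plan that is not shown, and silence in an article is no fault. What stands is that the method the article does name has this property.
- **The inflation is standard and correct.** Also true. A reader might infer from it that the plan has decided drop-outs contribute nothing to the analysis. It has not: the inflation sets how many to recruit and does not define the analysis set. It protects the planned 48.
- **Set point 5 may not be a separate level.** The article has only three distinct ventilation settings (30%/30, 100%/30 and 100%/45 mmHg). If those are the levels, a patient missing only set point 5 still has every level and is not dropped. The point holds if the set points themselves are the levels.
- **Few patients may stop in the last interval.** The article gives neither timing nor reasons for drop-out. Set points 4 and 5 are nominally about 5 minutes apart, plus the time to reach the new settings, and some drop-outs may occur before any reading. This limits the gain; it does not remove it.
- **The ANOVA is not a mistake, and power at 48 is adequate.** For 4 points with Tukey over five set points, power exceeds 0.8 once rho is 0.3 or more. With 24 per group, power for the 6-point anesthetic difference is about 0.91, above the stated 85%. The mixed model is therefore an improvement on the stated analysis, not the repair of an invalid one.

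**Conclusion.** The point holds as a low-cost improvement. The repeated measures ANOVA, run classically over the five set points, would discard complete primary readings from a patient who lacks only set point 5. The gain from keeping them is at most about 6% in the standard error of the primary contrasts, or about 0.07 in power. It shrinks roughly in proportion as fewer of the six expected drop-outs stop after set point 4. This rests on the classical form of the method, on the set points being the levels of ventilation strategy, on SD 6.2 and on an assumed rho. The sample size of 54 is not in question.

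A reader might go further and infer that a completers-only result is biased, because patients who tolerate 30% oxygen poorly would be lost and might respond most to oxygen. With an assumed response difference of 3 to 6 points, the shift would be 6/54 × 3 = 0.33 to 6/54 × 6 = 0.67 points. The documents do not support this. Nothing in them gives such a difference. Persistent low saturation on 30% oxygen is already covered by the withdraw-and-replace rule. It would usually appear at set point 1 or 2, before there is any FIO2 response for a model to recover. It could first appear at set point 5, but the article gives no sign that this is typical. No bias of a stated size is shown.

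**What to change.** In the Analysis section:
- State that all randomized patients with at least one set-point reading are analysed.
- Replace the repeated measures ANOVA with a linear mixed model having set point, anesthetic and their interaction as fixed effects and the patient as the repeated unit. Take the Tukey-adjusted contrasts between set points from that model. Naming set point as the factor also settles its levels.
- Report a completers-only analysis as a sensitivity analysis.

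In Methods/design or the Power section, state that readings taken before a patient leaves the sequence are kept, and that the reason and the last set point reached are recorded.

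The cost is wording, with no extra patients, no extra rSO2 or blood gas measurements, and no change to clinical management. The one downside is reliance on a missing-at-random assumption, which is weaker than what a completers-only analysis needs.

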#### Analysis

Data will be analyzed with a repeated measures two-way analysis of variance in which ventilation strategy is the within-subjects factor and anesthetic regimen is the between-subjects factor. Residuals will be assessed for normality and equal variances; if necessary, the analyses will be adjusted. The primary analysis will focus on the comparison between the ventilation strategies. A post hoc Tukey’s HSD procedure will be used to correct for all pairwise comparisons between ventilation strategies.

The effect of desflurane or propofol on cerebral desaturation and a possible differential response to changes in ventilation strategy will be evaluated as a secondary outcome measure. Analysis for the primary outcome will be adjusted if interaction effects between ventilation strategy and the anesthetic used are significant. A p value of <0.05 will be considered statistically significant.

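### The ventilation factor has undefined levels, and an all-pairs Tukey procedure is a poor vehicle for the two contrasts that carry the primary aim

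*Protocol article*

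**What the plan says.** Under Statistical considerations, Analysis, the model is fixed as follows: "Data will be analyzed with a repeated measures two-way analysis of variance in which ventilation strategy is the within-subjects factor", with anesthetic regimen between subjects. On inference it says "The primary analysis will focus on the comparison between the ventilation strategies" and "A post hoc Tukey’s HSD procedure will be used to correct for all pairwise comparisons between ventilation strategies". The assumption checks are "Residuals will be assessed for normality and equal variances; if necessary, the analyses will be adjusted". It adds a conditional rule: "Analysis for the primary outcome will be adjusted if interaction effects between ventilation strategy and the anesthetic used are significant".

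The levels of the within-subject factor are not listed. Methods/design gives five consecutive set points, the first being "1) FIO_2_ 30% (70% nitrogen), PETCO_2_ 30 mmHg – supine position". Points 2 to 5 are all in the beach chair position:

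- point 2: 30% / 30 mmHg
- point 3: 100% / 30 mmHg
- point 4: 100% / 45 mmHg
- point 5: 30% / 30 mmHg again

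The primary aim in Methods/design is confined to FIO2 and PETCO2 effects in the beach chair position.

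**The concern.** Points 1, 2 and 5 have the same gas setting. Point 1 differs from 2 in position, and point 5 differs from 2 in time and in what came between. Only 2 v 3 (FIO2) and 3 v 4 (PETCO2) isolate the two manipulations in the stated position. A test that all five means are equal is therefore not a test of ventilation, and Methods/design itself expects rSO2 to fall after positioning.

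Classical Tukey after a repeated measures ANOVA applies one pooled error to every pair. That is right only if all pairwise differences have the same variance (sphericity). Equal variance at each set point does not guarantee this: a serially correlated series has equal variances and still violates sphericity. The announced checks could pass while the standard errors are wrong.

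The last issue is the interaction rule. It lets the primary analysis change on a data-dependent test without saying how. The protocol chose the two agents partly because they differ in CO2 responsiveness, so an interaction is foreseeable.

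**Working it through.** **Inputs.** From Power: SD 6.2, 48 patients (24 per arm), expected effects of 6–8 points for FIO2 and 2–4 for PETCO2, power above 0.8 claimed for 4–5 points. From Analysis: significance level 0.05, taken as two-sided. Assumed, because the article does not give them: the within-patient correlation, the pooled error term, and a positioning effect of 3 points.

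**The plan's own figure.** The SE of a paired difference is 6.2·√(2(1−ρ)/48). Power for 4 and 5 points is:

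- 0.87 and 0.97, unadjusted, ρ = 0
- 0.66 and 0.88, Tukey over five levels, ρ = 0
- 0.81 and 0.96, Tukey, ρ = 0.25
- 0.96 and 0.998, Tukey, ρ = 0.5

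The claim reproduces, except at 4 points with Tukey and a correlation near zero.

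**Overall test.** Simulated trials had 24 + 24 patients, five set points, no gas effect, and a 3-point difference between point 1 and the rest. The five-level F test rejected in about 93% (AR(1) 0.7), 98% (0.8) and over 99.9% (0.9) of trials; separate runs agree at about 92–100%. In these runs a false Tukey rejection among the beach chair pairs occurred in about 3% of trials. Across models with patient-specific gas responses the range was 0.4–7%.

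Pooling points 1, 2 and 5 into one level does not help. One of three reference readings would be supine, so a positioning drop D shifts the FIO2 contrast by D/3 (1 point if D = 3).

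**Standard errors under AR(1) 0.8.** The variance of a difference at lag k is 2·6.2²·(1−0.8^k). For lags 1 to 4, 1−0.8^k is 0.200, 0.360, 0.488 and 0.590, with 4, 3, 2 and 1 pairs. The mean is (0.800 + 1.080 + 0.976 + 0.590)/10 = 0.345.

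- Pooled SE: √(76.88 × 0.345/48) = 0.743.
- Own SE for 2 v 3 or 3 v 4: √(76.88 × 0.200/48) = 0.566.
- Pooled/own ratio: 0.743/0.566 = 1.31. For 2 v 5 it is √(0.345/0.488) = 0.84.

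Simulated family-wise error is about 6.5%. Under compound symmetry every ratio is 1.00 and family-wise error is 5.0%.

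**Power for a 2-point PETCO2 effect (3 v 4).** The Tukey critical value is q(5, 184)/√2 = 2.755. Bonferroni over two contrasts uses t = 2.317 on 46 df. At AR(1) 0.8:

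- Pooled Tukey: threshold 2.755 × 0.743 = 2.047; Φ((2 − 2.047)/0.566) = 0.47.
- Own SE, two contrasts: threshold 2.317 × 0.566 = 1.311; Φ((2 − 1.311)/0.566) = 0.89.

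| Assumed correlation | Pooled Tukey, ten pairs | Own SE, Bonferroni over ten | Own SE, Bonferroni over two |
|---|---|---|---|
| AR(1) 0.7 | 28% | about 48% | about 72% |
| AR(1) 0.8 | 47% | about 72% | about 89% |
| Compound symmetry 0.7 | 55–56% | about 48% | about 72% |

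The middle column separates the two sources of gain. Under serial correlation both the standard error and the smaller family contribute. Under compound symmetry the whole gain comes from the smaller family.

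**At larger effects.** Pooled Tukey has 80% (AR(1) 0.7) and 95% (0.8) power at 3 points, and 99% or more at 4 points. At AR(1) 0.9 it already has 88–89% at 2 points.

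**The case against.** The best defense has four parts.

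- **The error term and correlation are not stated.** This stands. A reader might infer that the plan produces wrong standard errors. The documents do not support that: pooling is inferred from the name of the procedure, AR(1) is an assumption, and compound symmetry shows no fault. AR(1) is also imperfect here, since the readings are unequally spaced and points 2 and 5 share a condition. In models with patient-specific gas responses the pooled/own ratio for 2 v 3 ranged from 1.00 to 1.31.
- **The misstatement is conservative where it matters.** This stands for false positives in the AR(1) case. The contrasts with too small an error there, such as 2 v 5, carry no gas hypothesis. Conservatism still costs power at the low end of the PETCO2 range.
- **The overall F test is not the stated basis for inference.** This largely stands. The text puts the primary focus on comparisons between strategies, and the power statement concerns pairwise comparisons. A reader might infer that a significant F would be reported as proof of a ventilation effect; nothing in the article says so.
- **An article may leave sphericity, the error term and interaction handling to a fuller plan.** This is fair for a sphericity correction. Such a correction would mend the F test, but not the undefined factor levels, the all-pairs family or the open-ended interaction rule. That rule may mean no more than adding arm-specific results, so bias from it cannot be claimed.

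**Conclusion.** The concern holds in a limited form and should be fixed, but it does not invalidate the trial's primary result. The article itself establishes that the factor's levels are undefined, that three of the five set points share one gas setting, and that only 2 v 3 and 3 v 4 address the primary aim. With five levels, a significant overall test would not demonstrate a ventilation effect.

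The standard-error problem is conditional on a pooled error and on failure of sphericity. Under AR(1) 0.8 it is a 31% overstatement for the two key contrasts, with family-wise error near 6.5%; under compound symmetry it is nil.

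A reader might also infer that the stated power collapses. It does not: this defect leaves power at 4–5 points intact. The loss is confined to a PETCO2 effect near 2 points, and part of what the remedy recovers comes from correcting for two contrasts instead of ten.

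**What to change.** Define the factor's levels in the analysis text and make these changes:

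- Name 2 v 3 (FIO2) and 3 v 4 (PETCO2), both in the beach chair position, as the primary contrasts. Give each its own standard error, from paired differences within arm or from a mixed model with unstructured within-patient covariance, and correct for multiplicity over those two.
- Report 1 v 2 separately as the positioning effect and 2 v 5 as a check for time or carry-over.
- State that the overall F test is not evidence of a ventilation effect.
- Keep the equally weighted average of the two anesthetic arms as the primary estimate whatever the interaction p value, with arm-specific estimates as secondary.

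The cost is wording only: no change to sample size, data collection or conduct. The downside is that the remaining pairwise comparisons become secondary.
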